## Abstract

**Introduction:**

Obesity is a public health challenge worldwide. To maintain a healthy weight, dieting and lifestyle changes are the first-line interventions; however, these interventions are of poor compliance and may cause body composition changes, mainly skeletal muscle wasting (sarcopenia). Dietary supplements for improving body composition while inducing weight loss are therefore needed. β-hydroxy-β-methylbutyrate (HMB) has been proven to be effective for improving muscle mass and muscle strength in athletes, older adults and patients with cancer. We aim to evaluate the effectiveness and safety of HMB-enriched nutritional supplements for improving muscle mass and muscle function in obese adults during calorie restriction.

**Method and analysis:**

A total of 72 Chinese adults with obesity will be randomised to receive HMB-enriched nutritional supplements (65 g/day) or a placebo for 12 weeks. Participants in both groups will also receive calorie restrictions based on the individualised nutrition guidance of dietitians. Participants and investigators will be blinded to the allocations. The primary outcome will be the mean change in whole-body skeletal muscle mass (measured by bioelectrical impedance analysis). The secondary outcomes will include the mean change of appendicular skeletal muscle mass, body fat mass, basal metabolic rate, phase angle, muscle function and serum biomarkers. The enrolment will commence in December 2021 and will proceed until March 2022.

**Ethics and dissemination:**

This protocol has been approved by the Biomedical Ethics Committee of West China Hospital (2021-771). All potential subjects will be required to sign a written informed consent. The results of this study will be reported in peer-reviewed academic journals and conferences.

**Trial registration number:**

NCT04953936.

Strengths and limitations of this studyThis is the first randomised, double-blind, placebo-controlled trial to explore the possible effectiveness and safety of β-hydroxy-β-methylbutyrate (HMB)-enriched nutrition supplements for maintaining skeletal muscle mass and function in obese adults during calorie restriction.Using identical doses and appearance of HMB-enriched nutritional supplements and placebos to mask participants and outcome assessors.The hydration status of the participants may affect the results of the bioimpedance analysis.The sample size of this trial is relatively small.

## Introduction

Obesity is a chronic disease featured by abnormal or excess body fat that impairs health.^1^ Over the past three decades, obesity has become a common health problem that plagues modern people worldwide.^2^ For example, more than one-third (36.5%) of the US adult population is obese defined by a body mass index (BMI) ≥30 kg/m^2^.^3^ In China, the prevalence of abdominal obesity (defined by a waist circumference ≥90 and 85 cm for men and women, respectively) among adults is approximately 29%, and the number of adults with abdominal obesity (using the same definition) is approximately 277.8 million.^4^ Obesity is a risk factor for cardiovascular diseases, diabetes, dyslipidaemia, chronic kidney disease and some types of cancer, and increases the risk of psychological disorders, disability, poor quality of life and death.^1 2 5 6^ Therefore, obesity prevention and control have become one of the key contemporary public health challenges.^7^

It is well known that increasing physical activity and improving dietary strategies are the keys to the prevention and management of obesity.^1^ Many dietary strategies have been proposed for weight loss, such as very low energy diets, ketogenic diets, high-protein diets and high-fibre diets. However, individuals who apply these approaches may experience weight loss accompanied by body composition changes, mainly skeletal muscle wasting (sarcopenia).^3^ Sarcopenia may result in a lower resting metabolic rate and a greater tendency to regain body fat. Recently, there is growing evidence that certain nutritional fortifications can improve body composition during weight loss.^8^ A variety of over-the-counter dietary supplements for this purpose are available, and they have gained popularity among consumers for weight management.^9^

Leucine, a branched-chain essential amino acid, and its active metabolite β-hydroxy-β-methylbutyrate (HMB) play an important role in regulating protein synthesis in muscle cells, especially through activation of the mammalian target of rapamycin signal pathway.^10^ HMB can also suppress protein degradation pathways by inhibiting intracellular inflammation and caspase-8 activation.^11^ However, the rate of conversion of leucine to HMB is very low, and only approximately 5% of leucine in humans is converted to HMB.^12^ Studies have found that HMB has the effect of increasing muscle mass and reducing exercise injury.^13 14^ The tolerability and safety of HMB in humans have been well established.^15–17^ As early as 1995, the US Food and Drug Administration has listed HMB in ‘Generally Recognized as Safe’ ingredients. In 2010, China’s former Ministry of Health announced the approval of HMB as a ‘new resource food’, which refers to a newly developed, newly discovered or newly introduced food that is not traditionally consumed in China and that meets the basic requirements for food while being non-toxic and harmless to humans.

Studies have shown that HMB supplementation is also beneficial in building muscle strength and may be beneficial in improving body composition. For example, a systematic review that included seven randomised controlled trials (RCTs) showed that HMB supplementation was valuable for maintaining muscle mass in older adults and preventing muscle atrophy due to bed rest or other factors.^18^ Another systematic evaluation that included nine RCTs also showed that HMB supplementation improved body composition in older adults.^19^ Daily HMB supplementation is supposed to increase the benefits of exercise and improve body composition in healthy adults in the early stages of regular exercise.^20^ Therefore, HMB is expected to be a muscle-protective nutritional fortification that can effectively improve muscle mass and muscle strength in both healthy adults and the elderly. However, evidence regarding the effectiveness of HMB on maintaining skeletal muscle in obese adults during weight loss is limited in the literature. Additionally, very few clinical trials regarding HMB have been conducted in Chinese populations. Therefore, this trial aims to assess the effectiveness and safety of HMB-enriched nutritional supplements for improving muscle mass and muscle function in Chinese adults with obesity during the weight loss process using calorie restriction.

## Methods and analysis

### Study design

We designed a single-centre, randomised, parallel-group, double-blind, placebo-controlled trial. We plan to recruit 72 Chinese obese adults who intend to perform weight loss via calorie restriction. The participants will be randomly assigned to either the intervention group or the control group at a 1:1 ratio and will receive HMB-enriched nutritional supplements or placebo, respectively, for 12 weeks. The flow chart of this trial is presented in figure 1 while the overall schedule of this trial is shown in table 1.

**Figure 1 F1:**
[figure not shown]
Flow chart of this trial. HMB, β-hydroxy-β-methylbutyrate.

**Table 1 T1:** Schedule of enrolment, interventions and assessments

Timepoint	Enrolment	Allocation	Postallocation			
	Visit 1	Visit 2	Visit 3	Visit 4	Visit 5	Visit 6
	Screening (−4 to 0 week)	Baseline (0 week)	3 weeks±2 days	6 weeks±2 days	9 weeks±2 days	12 weeks±2 days
Enrolment						
Consent	√					
Inclusion and exclusion	√					
Demographics	√					
Medical history	√					
Body height	√					
Body weight	√					
Blood pressure	√					
Heart rate	√					
BIA	√					
Allocation		√				
Interventions*						
HMB nutritional supplement+calorie restriction						
Placebo+calorie restriction						
Assessments						
Inclusion and exclusion		√				
Body weight		√		√		√
Blood pressure		√		√		√
Heart rate		√		√		√
WC		√		√		√
HC		√		√		√
IPAQ-SF		√	√	√	√	√
FFQ		√	√	√	√	√
BIA		√		√		√
Sit-to-stand test		√		√		√
HGS		√		√		√
Blood tests†		√				√
Adverse events‡			√	√	√	√
Adherence‡			√	√	√	√

*Both intervention groups will also receive dietary instruction.

†The blood tests will include glucose metabolism (fasting glucose and insulin), albumin, haemoglobin, alanine aminotransferase, aspartate aminotransferase, gamma-glutamyl transpeptidase, cystatin C, creatinine, estimated glomerular filtration rate, lipid profiles and full blood counts.

‡Weekly WeChat or telephone contacts will be performed to assess adverse events and adherence (including dietary compliance).

BIA, bioimpedance analysis; FFQ, Food Frequency Questionnaire; HC, hip circumference; HGS, hand grip strength; HMB, β-hydroxy-β-methylbutyrate; IPAQ-SF, International Physical Activity Questionnaire Short Form; WC, waist circumference.

### Recruitment

This trial will be conducted at West China Hospital, Sichuan University, China. To reach the target sample size, we plan to advertise this trial using the hospital’s homepage, WeChat and flyers inside and outside the hospitals.

### Participants

#### Inclusion criteria

Individuals who meet all the following criteria will be invited to participate in this study: (1) men and women aged 30–50 years; (2) currently having obesity defined by BMI ≥28 kg/m^2^ (based on measured body weight (BW) and height at booking using validated scales)^21^; (3) having an intention to lose weight via calorie restriction; (4) healthy and able to walk independently; (5) able to eat independently to meet their energy needs; (6) without significant BW change in the last 6 months (less than 5% change in BW); (7) having sedentary habit defined by Sedentary Behavior Research Network^22^; (8) able to collaborate with the research staff. Individuals will be recruited by research nurses or physicians. The study protocol will be provided in advance and individuals who wish to participate will be offered the opportunity to discuss the study and consent to participate. All participants will be required to sign the written informed consent before participation.

#### Exclusion criteria

Individuals with any of the following criteria will be excluded: (1) a history of intolerance to enteral nutrition, food (eg, lactose intolerance) or being allergic to the components of the HMB-enriched nutritional supplements (eg, soy or corn); (2) having any implants (eg, pacemakers, implantable cardioverter defibrillators and dental implants); (3) current use of other nutritional supplements or drugs that may have an impact on the effectiveness of the intervention (eg, glucocorticoids, antineoplastic drugs, antituberculosis drugs, sedatives, antipsychotics, muscle relaxants, monoamine oxidase inhibitors, antibiotics) within 3 months prior to enrolment; (4) secondary obesity caused by diseases (eg, hypothalamic diseases and hypercortisolism) or drugs (eg, glucocorticoids, insulin, tricyclic antidepressants and weight loss supplements/drugs); (5) clinically visible oedema; (6) trauma, surgery, hospitalisation, fall or fracture within 6 months prior to enrolment; (7) pregnancy, having pregnancy plans or lactation; (8) individuals who are participating in other clinical trials; (9) any acute illness (eg, acute infection, myocardial infarction, arrhythmia, myocarditis, appendicitis, etc); (10) swallowing disorders; (11) abnormal thyroid function (including hyperthyroidism and hypothyroidism); (12) history of diabetes, respiratory diseases, cardiovascular diseases, uncontrolled hypertension, kidney diseases, digestive system diseases, renal insufficiency, mental illness, neurological diseases, haematologic diseases, liver diseases (except for fatty liver), chronic infection (eg, tuberculosis), immune system diseases, joint disorders, any type of tumour; (13) alcohol consumption over two standard alcoholic beverages (20 g of alcohol/day); (14) menopause women; (15) difficulty to comply with the study protocol; and (16) other conditions that indicate the individuals are inappropriate for participation in this study.

#### Withdrawal criteria

We will withdraw participants from this trial after randomisation for the following reasons: (1) if the participants request to withdraw from this trial; (2) if there is evidence of a complication or the occurrence of an unknown disease, the investigators can decide that the patient cannot continue in the study; (3) if there is an adverse event (AE) classified as grade 3 or higher according to the Common Terminology Criteria for Adverse Events (CTCAE) version 5.0; (4) if investigators believe the participants are unsuitable for continuing participating in the study for any other reason.

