#### Safety outcomes

We will record all AEs during the entire study period. The participants will be asked to complete a self-reported questionnaire regarding any AE every 3 weeks. The participants will also be encouraged to report AEs to the research staff via telephone when there is any AE occurrence. We will rank the severity of AEs according to the CTCAE version 5.0. The cause of the AEs will be ranked as unknown, definitely not related, probably not related, possibly related, probably related and definitely related.^29^

Moreover, we will report the mean change in the laboratory tests regarding AEs from the beginning to the end of the 12-week intervention: haemoglobin, AST, ALT, GGT, cystatin C, creatinine and eGFR.

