### Statistical analysis plan

The statistical analysis will be performed by an independent statistical expert blinded to the group allocation. SPSS V.26.0 (IBM) and R V.4.0.3 (R Foundation for Statistical Computing, Vienna, Austria) will be used for statistical analysis.

Each group will be summarised in terms of demographic characteristics and baseline variables. For comparisons of continuous variables, two-sample t-tests or Mann-Whitney U tests will be used, whereas for categorical variables, the χ^2^ test or Fisher’s exact test will be used.

As aforementioned, the primary outcome will be in SMM from the beginning to the end of the 12-week intervention. The independent two-sample t-test or Mann-Whitney U test will be used based on the distributional normality. We will make adjustments based on the covariates if there are significant demographic differences between the groups or if baseline variables differ significantly. In the primary analysis, the full analysis set (FAS) will be the main data set. Participants initially assigned to either group will be included in the FAS. However, our analysis will not use the data of ineligible participants (ie, those who are wrongly enrolled because of measurement or human error), subjects who received less than 75% of the planned intervention or subjects without the primary outcome measurement. For sensitivity analysis, we will use a protocol-specific set to compare with the results from the FAS. A per-protocol analysis will include participants who achieved the completion of the study without major deviations from protocol, who provided the primary outcome and who received at least 75% of the planned intervention. The rate of protocol compliance in each group will be calculated. A significance level of two-sided p<0.05 will be used. If needed, the multiple imputation method will be adopted for missing data.

We will use the same methods for analysing secondary outcomes as we did for analysing the primary outcome. A paired t-test or Wilcoxon signed-rank test will be used to assess the changes in outcome measures within groups before and after the intervention. To validate trend differences per visit, we will use repeated measures analysis of variance with post hoc tests.

Moreover, subgroup analysis will be done to identify whether gender or Asian Working Group on Sarcopenia-defined sarcopenia^30^ at baseline would affect the clinical response to HMB-enriched nutritional supplements.

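### Withdrawal is from the trial itself, and the analysis-set rules then exclude those withdrawn, so efficacy outcomes of participants who tolerate the product worst are missing from both the primary and the sensitivity analysis

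*Protocol article*

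**What the plan says.** **Withdrawal.** The Withdrawal criteria section opens with "We will withdraw participants from this trial after randomisation for the following reasons". The four reasons are the participant's request ("if the participants request to withdraw from this trial"), a complication or unknown disease after which "the investigators can decide that the patient cannot continue in the study", a severe event ("if there is an adverse event (AE) classified as grade 3 or higher"), and any other reason the investigators find sufficient. All four are worded as leaving the trial or study. No status of being off product but still followed is defined.

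**Analysis sets.** The Statistical analysis plan section first states "Participants initially assigned to either group will be included in the FAS". It then says "our analysis will not use the data of ineligible participants", and the same sentence extends this to "subjects who received less than 75% of the planned intervention or subjects without the primary outcome measurement". The per-protocol set, used for sensitivity, again requires the 75% and the primary outcome, and adds completion with no major protocol deviation. Secondary outcomes follow the primary outcome's methods. Multiple imputation is available if needed.

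**Measurement.** The primary outcome is the change in skeletal muscle mass (SMM) to week 12. Table 1 schedules body composition at baseline, week 6 and week 12, and blood tests after baseline only at week 12. On laboratory safety, the Safety outcomes section says "we will report the mean change in the laboratory tests regarding AEs from the beginning to the end of the 12-week intervention". The same section has all adverse events recorded throughout the study and graded.

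**The concern.** Two rules that each look routine act together. The first ends measurement for people who leave for reasons linked to tolerance. The second removes the same people from the analysis. Whether someone is withdrawn, or reaches 75% of the intervention, is decided after randomisation and can depend on the product taken. The arms receive quite different powders: a multi-ingredient protein, oil and fibre product against maltodextrin. Tolerance may therefore differ by arm, and the groups left for comparison need no longer be the groups that randomisation made.

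At stake are the size of the effect on SMM, and possibly its significance, in a trial that means to inform larger ones. A sensitivity analysis should expose such a problem, but this one cannot, because it applies the same two filters. Outcomes never measured cannot be recovered later by any analysis plan.

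**Working it through.** **1. Which exclusion catches whom.** The intervention lasts 12 weeks, one dose daily, so 84 doses. The threshold is 0.75 × 12 = 9 weeks, or 0.75 × 84 = 63 doses.

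| Time of withdrawal | 75% rule | Week-12 SMM | In FAS | In per-protocol set |
|---|---|---|---|---|
| Before about week 9 | fails | none described | no | no |
| About week 9 to before week 12 | may pass | none described | no | no |

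Week 9 is therefore not the operative boundary. Any withdrawal before the week-12 visit leads to exclusion by one route or the other. Data already collected can also go: someone withdrawn at week 8 (8/12 = 67%) has a week-6 body composition measurement, but fails the 75% rule, which carries over if the same methods for secondary outcomes include the same analysis set.

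**2. Internal consistency.** All assigned participants cannot be in the FAS while those below 75% or lacking the outcome are left out. Imputing a missing primary outcome has no one to act on if everyone without it is already excluded.

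**3. The plan's sample size.** Inputs: standardised effect d = 0.93, two-sided 5%, 80% power, 25% attrition, stated total 70, raised to 72.
- Normal approximation: n per arm = 2 × (1.960 + 0.842)² / 0.93² = 18.2, so 19. The t-test needs 20.
- Total with attrition: 40 / 0.75 = 53.3, so 54. The stated 70 is not reproduced. It does result from 90% power (26 per arm, 52 / 0.75 = 69.3, so 70).

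The stated total exceeds what its inputs need, so this is a separate matter. It helps here because it leaves room for an all-randomised analysis.

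**4. Numbers at risk.** The plan's 25% attrition gives 0.25 × 72 = 18 participants, leaving 54 (27 per arm if balanced). This is loss from all causes, not intolerance alone. At d = 0.93 the t-test has 91.8% power with 27 per arm and 97.3% with 36.

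**5. Overstatement of the effect (illustration).** Assume that a share q of the active arm stops and gains nothing, the rest gain 0.93 SD, and the SD is unchanged. The all-randomised effect is 0.93 × (1 − q), and analysing only those who stay overstates it by 1/(1 − q) − 1.

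| q (assumed) | All-randomised d | Overstatement | Power, 36 per arm |
|---|---|---|---|
| 10% | 0.837 | 11% | 93.8% |
| 20% | 0.744 | 25% | 87.6% |
| 25% | 0.698 | 33% | 83.1% |

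**6. False-positive rate (illustration).** Assume no product effect. A share q of the active arm is excluded, its 12-week change is δ SD worse than that of those retained, and no one is excluded from the control arm. Bias = qδ, SE = √[1/(36(1 − q)) + 1/36], and the rejection rate is 1 − Φ(1.96 − bias/SE) + Φ(−1.96 − bias/SE). For q = 25% and δ = 0.5: bias 0.125, SE = √(1/27 + 1/36) = 0.255, rejection rate 7.8%.

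| q | δ = 0.5 | δ = 1.0 |
|---|---|---|
| 10% | 5.5% | 7.0% |
| 15% | 6.1% | 9.4% |
| 25% | 7.8% | 16.6% |

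Exclusion in one arm only is the unfavourable case. If the same kind of participant leaves both arms equally often, this bias cancels.

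**7. Safety laboratory tests.** With blood drawn only at baseline and week 12, a participant who leaves earlier has no scheduled post-baseline value.

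**The case against.** The strongest opposing case concerns safety, and it largely stands. A reader might infer that adverse events of those withdrawn are lost; for example, that 3 grade 3 events among 36 active participants would be reported as 0 of 33. The documents do not support this. Adverse events are recorded over the whole study by three-weekly questionnaire and telephone report, with weekly contact under Data collection, management and monitoring. A grade 3 event must be recorded and graded before it can trigger withdrawal. Reasons for dropping out are kept as a feasibility outcome. The exclusions stand in the primary-outcome paragraph and are extended only to secondary outcomes; safety outcomes have their own heading. The count of 3 has no source either. What remains is that the exclusion sentence is worded without limit, and one clause would close that.

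It can also be said that a safety population, tables of graded laboratory values and detailed follow-up procedures belong in a full protocol or statistical analysis plan, which are not shown. That is right, and their absence is not part of this point. The point rests on rules the article does state: withdrawal from the trial, and exclusion from the FAS.

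A reader might further infer that everyone who stops the product is withdrawn. The text does not say so. Stopping product alone is not a listed reason, and those who miss visits are contacted to encourage attendance. Such a person could complete follow-up and have a week-12 measurement, yet the 75% rule would still discard it.

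Finally, it may be argued that the defect lies only in the FAS definition. Correcting that alone would leave those withdrawn with nothing but imputed week-12 values, so both sections matter.

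**Conclusion.** The point holds for efficacy. Read together, the withdrawal rule and the two FAS exclusions remove participants on post-randomisation events that the product can influence, and the per-protocol set repeats the filter. The FAS sentences also contradict each other.

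For safety, only the week-12 blood test is clearly missed by those withdrawn earlier. Adverse events are recorded, and the text does not apply the 75% rule to them.

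The size cannot be fixed from the documents, which give neither the share who would be withdrawn nor their outcomes. Under the assumptions shown, the all-randomised effect is overstated by 11% to 33%. Across the cases tabulated, the false-positive rate is 5.5% to 16.6% instead of 5%, the upper figure needing a quarter of one arm lost with outcomes a full SD worse. If withdrawals are few, or alike in both arms, the bias is small. The conclusion also assumes that withdrawal from the trial means no later measurement, which is the natural reading but is not stated outright. This should be corrected; it does not invalidate the trial. No view is taken on the clinical stopping criteria.

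**What to change.** 1. Leave the clinical stopping criteria unchanged. In the Withdrawal criteria section, separate stopping study product from withdrawing consent to follow-up.
2. Ask those who stop product to attend the existing week-6 and week-12 visits, including the week-12 blood test, and keep their data.
3. Remove the 75% and missing-outcome exclusions from the FAS. Keep the 75% rule for the per-protocol set only.
4. Use the multiple imputation already named for outcomes still missing. It cannot fully repair losses related to outcome, so step 2 comes first.
5. State that the exclusions in the Statistical analysis plan section do not apply to adverse-event reporting.

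Cost: an amendment to protocol and consent wording, with the ethics re-approval the article requires, and some effort to follow people who are off product. No visits are added. The estimated effect may be smaller, because it then describes everyone randomised. With 36 per arm fully followed, power stays at 83.1% even in the 25% dilution case above.
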